## Abstract

**Introduction:**

Utidelone (UTD1) is a new chemotherapeutic drug for recurrent or metastatic breast cancer. However, it usually leads to severe peripheral neuropathy (PN) and causes numbness of the hands and feet and significant pain in patients' life. Electroacupuncture (EA) is considered beneficial in improving PN and relieving numbness of the hands and feet. This trial aims to evaluate the therapeutic effect of EA on PN caused by UTD1 in patients with advanced breast cancer.

**Methods and analysis:**

This study is a prospective randomized controlled trial. A total of 70 patients with PN caused by UTD1 will be randomly assigned to the EA treatment group and the control group in a ratio of 1:1. The patients in the EA treatment group will receive 2 Hz EA three times a week for 4 weeks. The patients in the control group will take mecobalamin (MeCbl) tablets orally, one tablet each, three times a day for 4 weeks. The main outcome measures will be the evaluation scale of peripheral neurotoxicity of chemotherapeutic drugs according to the European Organization for Research and Treatment of Cancer Quality of Life Questionnaire-CIPN 20-item (EORTC QLQ-CIPN20) and the peripheral neurotoxicity assessment rating according to NCI CTCAE version 5.0. Secondary outcomes will be the quality of life scale according to the European Organization for Research and Treatment of Cancer Core Quality of Life Questionnaire (EORTC QLQ-C30). The results will be evaluated at baseline, post-treatment phase, and follow-up. All major analyses will be based on the intention-to-treat principle.

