### Primary outcome

#### The evaluation scale of peripheral neurotoxicity of chemotherapeutic drugs according to EORTC QLQ-CIPN20

There are 20 items in the questionnaire, including 9 items in the subscale of sensory nerve symptoms (involving tingling, numbness, pain, walking or standing instability, temperature perception, and hearing), 8 items in the motor nerve symptom subscale (involving spasm writing, manipulation of small objects, and weakness), and 3 items in the autonomic nervous symptom subscale (involving vision, vertigo after changing posture, and erectile dysfunction) (26). The scoring method is the same as that of other QLQ scales. All items are scored with four levels: “no, a little, quite, and very,” respectively, assigned 1–4 points. After standardizing the scores of each dimension according to the scoring requirements, the score range of each dimension is 0–100 points. The higher the score, the more the severe CIPN symptoms. At present, the reliability and validity of the tool have been tested to a certain extent in some countries (27, 28), and it has been applied to corresponding studies (29, 30).

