#### Peripheral neurotoxicity grades will be assessed according to NCI CTCAE version 5.0

This outcome will be determined by the professional evaluator according to the symptoms of PN in the patient, including checking the degree of peripheral nerve damage of the participant, such as muscle strength and muscle tension. In grade I, slight sensory numbness or tendon reflex disappeared, with no function affected. Grade II includes moderate sensory numbness or sensory loss, which affects function but does not affect daily life. Grade III includes significant sensory numbness or sensory loss, which affects daily life. Grade IV includes sensory-motor neuropathy, which severely interferes with daily life (31).

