### Secondary outcome

#### The quality of life scale according to EORTC QLQ-C30

The European Organization for Research and Treatment of Cancer QLQ-C30 is a quality-of-life instrument for use in international clinical trials in oncology (32). QLQ-C30 scale includes five functional subscales, three symptom subscales, six single symptom measurement items, and one overall health subscale. The higher the functional subscale score, the better the quality of life, and the higher the symptom subscale score, the worse the quality of life.

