### Statistical analysis

The outcome data will be analyzed by the Statistical Package for the Social Sciences (SPSS) version 26.0 statistical software package. The researchers conducting data analysis will not know the distribution of participants and treatment methods. Categorical data will be displayed as counts and percentages. Numerical data of normal distribution will be expressed as mean ± standard deviations, while data of non-normal distribution will be expressed as median, minimum value, and maximum value of 95% confidence intervals. To compare the two independent samples, the *t*-test will be used to determine the numerical data of normal distribution, while the non-parametric test will be used to determine the data of non-normal distribution. The chi-square test or non-parametric tests will be used to determine categorical data. All hypothesis tests will be bilateral, with the level of significance established at 0.05.

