At present, there are no definite tools for evaluating the PN caused by UTD1. A numeric rating scale (NRS) for cancer pain has been applied to the clinical evaluation of various pain degrees since 1950 (42). The number between 0 and 10 is used to represent the pain intensity, which is applicable to the elderly and those with low educational levels person (43). However, due to its low sensitivity, it is rarely used to evaluate the degree of CIPN. The evaluation scale of EORTC QLQ-CIPN20 is a patient-self-reported questionnaire (26). As doctors and patients have different understandings of the disease, different evaluation results of CIPN may result. Especially when it comes to sensory disorders, there are significant differences between the two groups. Therefore, a reliable assessment of the severity of CIPN-related sensory disorders should combine clinical symptoms with a professional assessment. Peripheral NCV is commonly used to evaluate the degree of peripheral nerve damage. However, as our study subjects are patients with advanced breast cancer, NCV tests may cause discomfort to patients or increase their psychological burden. Therefore, we may recommend this test to patients who are willing, but it will not be used as the outcome of our study. In this study, the severity of PN caused by UTD1 will be evaluated using the evaluation scale of peripheral neurotoxicity of chemotherapeutic drugs according to EORTC QLQ-CIPN20 as the main outcome. To evaluate the accuracy, the professional evaluator will also comprehensively evaluate the peripheral neurotoxicity severity of the patient according to the patient's clinical symptoms and physical examination of the peripheral nervous system, and the severity grade will be determined according to NCCN5.0. In addition, the patient's quality of life will be evaluated according to EORTC QLQ-C30, and AEs during the study will be recorded, which will make the study results more convincing.

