Utidelone is mainly used for patients with recurrent or metastatic advanced breast cancer. These patients mainly have accumulated neurotoxicity of chemotherapeutic drugs in their bodies because they previously used large doses of anthracycline and taxus drugs. UTD1 may induce neurotoxicity accumulated by other chemotherapeutic drugs, or it may itself be a pathogenic drug that causes severe PN symptoms, but in either case, the patients who developed PN symptoms are related to UTD1, thus our research theme is consistent. The severity of PN symptoms caused by UTD1 is closely related to drug dose accumulation. The PN symptoms of patients who used UTD1 in the first few times are usually not serious, and these patients' symptoms can be relieved during the interval of chemotherapy, so they usually do not want other interventions. However, with the increase in chemotherapy times, the PN symptoms of patients become more serious. Their symptoms cannot be relieved during the chemotherapy interval, and they feel numbness and discomfort at the end of the limbs all the time. PN caused by UTD1 is mainly characterized by numbness, tingling, or other abnormal feelings in the hands and feet. Generally, the first symptom that patients experience is sensory nerve damage. However, patients who have used chemotherapy for UTD1 often develop motor nerve function damage. In particular, patients have weakness in both lower limbs and difficulty walking, some patients may also have muscle atrophy, but autonomic nerve function is rarely affected. It is highlighted here that sensory nerve symptoms are the most common in patients. Therefore, patients with only sensory nerve symptoms, such as patients with a certain degree of numbness, will be included in this study. During the recruitment, the doctors will evaluate the symptoms of PN according to the patient's condition. For the patient's simple numbness of individual fingers, perhaps the symptom of nerve compression, we will identify it clinically.

This study will clarify the efficacy of EA in the treatment of PN caused by UTD1 and provide technical guidance for clinical treatment. The results will further provide new clues, new ideas, and new methods for acupuncture in the treatment of nervous system diseases and cancer-related diseases. Finally, we hope the results of this study will effectively improve the PN symptoms caused by UTD1 in patients with advanced breast cancer, reduce their pain, and improve their quality of life.

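### The primary outcome is two measures in the Abstract and Methods but one in the Discussion, with no score or visit designated, so the false-positive rate of the main claim is uncontrolled

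*Protocol article*

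**What the plan says.** Three parts of the protocol article define the main outcome, and they do not agree.

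- **Abstract, Methods and analysis.** The outcomes are plural: "The main outcome measures will be the evaluation scale of peripheral neurotoxicity of chemotherapeutic drugs" according to EORTC QLQ-CIPN20, "and the peripheral neurotoxicity assessment rating according to NCI CTCAE version 5.0".
- **Methods, Primary outcome.** Two subheadings stand here, before a separate Secondary outcome heading. The first is CIPN20. The second reads "Peripheral neurotoxicity grades will be assessed according to NCI CTCAE version 5.0".
- **Discussion.** Severity will be evaluated "according to EORTC QLQ-CIPN20 as the main outcome", in the singular. The clinician's grade is added as a check on accuracy.

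The Outcome measures paragraph lists CIPN20, CTCAE grade and QLQ-C30 with no order among them. Hypothesis 1 mentions CIPN20 only as an example of a subjective outcome.

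On scoring, the article describes sensory, motor and autonomic subscales of CIPN20 and a 0 to 100 range for each: "After standardizing the scores of each dimension according to the scoring requirements". It names neither a total score nor a lead subscale. Table 1 and Study procedure set assessments at baseline, week 4 and week 8, and neither later visit is called primary.

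Statistical analysis gives one rule for all tests: "All hypothesis tests will be bilateral, with the level of significance established at 0.05".

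**The concern.** A trial's main claim has a defined false-positive rate only if the reader can tell in advance which result decides it. Here the named outcomes number one or two, depending on the section. Even on the narrower reading, CIPN20 could be represented by any of three subscales at either of two visits. If the deciding comparison is chosen after the data are seen, the 0.05 level no longer describes the risk of a false claim.

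The two named outcomes may well give different answers. The Discussion says that doctors and patients can assess neuropathy differently, above all for sensory disorders. Under Blinding, participants know their treatment while outcome assessors do not. CIPN20 is therefore self-report from unblinded patients, and the CTCAE grade comes from a blinded assessor. A split result is plausible, and the article does not say how it would be read.

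Calling the trial a pilot does not remove the issue. The Abstract says the results will help to prove whether electroacupuncture is effective and safe, and the Discussion says the study will clarify its efficacy.

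**Working it through.** **Inputs from the article**

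- Named main outcomes: 2 (Abstract; Primary outcome) or 1 (Discussion).
- CIPN20 dimension scores: 3. CTCAE grade: 1.
- Post-baseline visits: 2 (weeks 4 and 8).
- Level of each test: 0.05, two-sided.
- Sample size: 35 per group.

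The article gives no correlations between outcomes or visits, so values from 0.3 to 0.9 are assumed. It states no overall error rate, so there is no figure of its own to reproduce beyond 0.05 for a single test.

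**Number of comparisons**

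- Two named outcomes, one score each, one visit: 2.
- CIPN20 alone: 3 × 2 = 6.
- CIPN20 and CTCAE grade: (3 + 1) × 2 = 8.

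**Chance of at least one false positive if any single success counts**

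For k independent tests the rate is 1 − 0.95^k:

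- k = 2: 1 − 0.95² = 0.0975
- k = 6: 1 − 0.95⁶ = 0.265
- k = 8: 1 − 0.95⁸ = 0.337

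The correlated cases come from simulating equally correlated normal test statistics (500,000 draws).

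| Comparisons | Independent | r = 0.3 | r = 0.5 | r = 0.7 | r = 0.9 |
|---|---|---|---|---|---|
| 2 | 9.75% | 9.5% | 9.0% | 8.4% | 7.1% |
| 6 | 26.5% | 24.0% | 20.8% | 16.4% | 10.8% |
| 8 | 33.7% | 29.9% | 25.0% | 19.1% | 11.9% |

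With separate correlations between outcomes (0.3 to 0.7) and between visits (0.5 to 0.8), the eight-comparison rate is 19.6% to 29.8%, inside the same range.

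**Direction.** These rates count errors either way. Counting only false claims in favour of electroacupuncture, eight independent tests give 1 − 0.975⁸ = 18.3%, and the correlated cases give 15.2% (r = 0.3) down to 6.0% (r = 0.9). The comparable rate for one test is 2.5%.

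**Rules that control the rate**

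- One score at one visit: 5%.
- Both named outcomes must be significant at 0.05, one score each at one visit: at most 5%. With no effect on either, 0.05² = 0.25% if independent, and 0.5% to 3.0% for r from 0.3 to 0.9.
- Either may succeed, each tested at 0.025: at most 5%.

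**Cost in power.** For a numeric score with 35 per group and 80% power, the detectable difference in SD units is about (z for the two-sided level + 0.842) × √(2/35), where √(2/35) = 0.239:

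- level 0.05: (1.960 + 0.842) × 0.239 = 0.67 SD
- level 0.025: (2.241 + 0.842) × 0.239 = 0.74 SD
- level 0.05/8 = 0.00625: (2.734 + 0.842) × 0.239 = 0.86 SD (0.855 before rounding)

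**The case against.** A reader might infer that the plan has been shown to run a false-positive rate well above 5%. The article does not support that. The inflated figures apply only if any one success is allowed to carry the claim, and no section says so. If both outcomes had to succeed, or one CIPN20 score at one visit decided, the rate would be 5% or less. This objection stands: the rate is undefined, not shown to be high.

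The count of eight can also be challenged. The CIPN20 text explains how the questionnaire is scored, and Table 1 is an assessment schedule. Neither says that each subscale at each visit is a separate primary test. This stands too, so eight is the upper end of what the wording leaves open. The count closest to the explicit text is two.

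A further objection is that a condensed article may leave the score, visit and success rule to a full protocol or analysis plan that is not shown. Silence on those details alone would be no finding. The disagreement between the Abstract and Primary outcome section on one side and the Discussion on the other is different. It is on the page, and any later document would have to depart from one of them.

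A reader might also count the QLQ-C30 scales, described as "five functional subscales, three symptom subscales, six single symptom measurement items, and one overall health subscale", as raising the error rate of the main claim. They do not, because QLQ-C30 is a secondary outcome throughout.

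**Conclusion.** The point holds as an inconsistency that leaves the error rate of the main claim uncontrolled. The article names two primary outcomes in the Abstract and Methods and one in the Discussion, designates no CIPN20 score or visit, and applies 0.05 to every test.

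The size depends on a rule that the article does not state. If either named outcome at one visit can carry the claim, the excess over 5% is moderate; if any score at any visit can, it is large. The low ends of the ranges rest on an assumed correlation of 0.9 and the upper limits on independence. Neither can be checked from the article.

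**What to change.** Before analysis, bring the Abstract, Outcome measures, Primary outcome and Discussion into agreement in one of two ways.

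- **(a) One primary.** Name one score at one visit, for example the CIPN20 sensory subscale at week 4, tested at two-sided 0.05. This agrees with the Discussion, which treats CIPN20 as the main outcome and adds: "It is highlighted here that sensory nerve symptoms are the most common in patients". CTCAE grade, the other subscales and all week 8 values become secondary.
- **(b) Two primaries with a rule.** Keep CIPN20 (one named score, one named visit) and CTCAE grade at the same visit. State either that both must be significant at 0.05, or that each is tested at 0.025 and either may succeed. This fits the Discussion's view that self-report should be combined with professional assessment.

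Under both options, report the QLQ-C30 scales as secondary estimates with 95% confidence intervals.

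The change is one of wording, but each option has a price. Under (a), a benefit seen only on motor symptoms, only on CTCAE grade or only at week 8 cannot carry the main claim, and that claim rests on self-report from unblinded patients. The Discussion also says that motor damage often develops, so the choice of subscale deserves a stated reason. Under (b), power is somewhat lower. With the split level the detectable difference on a numeric score rises from about 0.67 to 0.74 SD; with the both-must-succeed rule, power is at most that of the weaker of the two outcomes.

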**Ethics and dissemination:**

This protocol was approved by the Medical Ethics Committee of Zhejiang Cancer Hospital on 26 July 2022. The license number is IRB-2022-425. This study will provide clinical efficacy data on EA in the treatment of PN caused by UTD1 and will help to prove whether EA is an effective and safe therapy. The study results will be shared with healthcare professionals through the publication of manuscripts and conference reports.

**Trial registration number:**

ChiCTR2200062741.

## Background

Recent data from the international agency for research on cancer showed that the incidence of breast cancer has exceeded that of lung cancer, with the highest incidence rate (1). The treatment of breast cancer includes surgery, chemotherapy, radiotherapy, targeted therapy, endocrine therapy, immunotherapy, and other methods (2). However, chemotherapy plays an irreplaceable role in the treatment of breast cancer because of its remarkable efficacy in systematic treatment, especially for patients with advanced breast cancer. However, a series of adverse reactions or side effects after chemotherapy should be paid greater attention. Chemotherapy-induced peripheral neuropathy (CIPN) is a common side effect of many chemotherapeutic drugs, especially in platinum compounds (e.g., cisplatin, carboplatin, and oxaliplatin), taxanes (e.g., paclitaxel, docetaxel, and albumin paclitaxel), anthracyclines (e.g., doxorubicin, epirubicin, and liposome doxorubicin), vinblastine, and other chemotherapeutic drugs (3). It is mainly manifested as limb numbness or abnormal sensation (e.g., as an ant crawling sensation and foreign body sensation), even loss of sensation or abnormal pain, and decreased tendon reflexes (4, 5). Antioxidants, neuroprotective agents or nutritive agents, and antiepileptic drugs are commonly used to treat CIPN, but they may bring other side effects or unsatisfactory efficacy (3, 6). CIPN symptoms can last for months or even years, not only affecting the progress and effect of cancer treatment but also easily causing emotional instability in patients, which seriously affects their life quality.

Utidelone (UTD1) is a new chemotherapeutic drug in recent years. It is a novel microtubule stabilizing agent and is an epothilone B analog that was produced by genetic engineering. It shows a wide range of antitumor activities in solid tumors (7, 8). At present, UTD1 is mainly used to treat recurrent or metastatic breast cancer (9), especially in patients who need high-dose anthracycline and taxus drugs or who develop resistance to them (10, 11). Some studies have shown that patients with advanced breast cancer who used UTD1 combined with capecitabine chemotherapy can prolong the 4-month survival time compared with capecitabine chemotherapy alone (10, 12). However, the main side effect of UTD1 is severe peripheral neuropathy (PN) (8). It can cause patients severe numbness of hands and feet, and some patients also feel discomfort such as sore limbs and pain. According to the literature, the incidence of PN caused by UTD1 combined with capecitabine is 85.4%, and the incidence of grade 3 CIPN is as high as 25.1%. Compared with capecitabine alone, the incidence of CIPN is 9.2%, and the incidence of grade 3 CIPN is <1% (10). Therefore, UTD1 can more easily lead to severe PN. Severe PN caused by UTD1 may reduce or withdraw from chemotherapeutic drugs and affect clinical efficacy. However, at present, there are few prevention and treatment schemes for severe PN caused by UTD1. Only one study pointed out that (11) ganglioside monosialic acid GM1 may reduce the severe PN induced by UTD1 plus capecitabine in metastatic breast cancer, but further research is still needed. Therefore, there is an urgent need for a treatment scheme that can effectively alleviate PN caused by UTD1 to improve the quality of life of patients with advanced breast cancer.

Acupuncture, as an important part of traditional Chinese medicine, has played an essential role in treating cancer-related diseases, especially in preventing and treating the side effects of chemotherapy (13, 14). Some studies have shown that acupuncture could effectively treat PN caused by various diseases, improve peripheral nerve conduction velocity (NCV), and alleviate patients' symptoms such as numbness, pain, or paresthesia of limbs (15). Acupuncture is also considered effective and safe in treating CIPN (16), with a better overall curative effect than that neurotrophic drugs (17). Electroacupuncture (EA) is a new acupuncture technology that combines traditional acupuncture technology with electrical stimulation, which has been widely used in treating nervous system diseases. Many studies showed that EA therapy could effectively treat CIPN and relieve numbness or pain in the hands and feet caused by chemotherapeutic drugs (18, 19). Animal experiments showed that low-frequency EA was more effective than high-frequency EA in alleviating CIPN symptoms (20). Stimulation with 2 Hz EA could reduce the mechanical pain and hyperalgesia of CIPN induced by paclitaxel in rats (21, 22) and also had a pronounced therapeutic effect on CIPN induced by oxaliplatin in rats (23). However, there is no study report about the efficacy of EA in the treatment of PN caused by UTD1. Whether EA can alleviate the numbness and pain in the hands and feet caused by UTD1 is unknown. Therefore, we designed a pilot RCT to evaluate the efficacy of EA on PN caused by UTD1.

The research will be a pilot clinical study. As there is no effective data on the study of EA treatment of CIPN, and considering that UTD1 is newly listed in China, only one of our cancer hospitals can use it in the whole province. We hope to collect as many cases as possible, but considering that there is a lack of large sample patients in the clinic, not all patients using UTD1 can be included in this study. We cannot set up a large sample size of controlled studies or multicenter studies. Therefore, we preliminarily plan to collect 35 cases in each group according to the minimum sample size of the clinical prospective trial.

